**(3) Reporting Methods**

A. Adverse events from SS-PDS arm that are serious, unpredicted and in causal relationship (SS-PDS SUSAR) : Investigators will take below measures in 7 days from the day they became aware of such adverse events.

A) Report to IRB of the applicable institution;

B) Report to the principal investigator: KGOG which is delegated by the principal investigator will report to MFDS in 7 days from the day such adverse events were reported and deliver the information to other institutions so that such adverse events are reported to IRBs the institutions, respectively.

C) However, such adverse events should be directly reported to the principal investigator events if they lead to death or are life-threatening.

B. Adverse events that are not SS-PDS SUSAR

A) KGOG which is delegated by the principal investigator will collect all adverse events from all participating institutions once a year and report to IRBs of all the participating institutions.

B) Adverse events that are not SS-PDS SUSAR can also be reported to IRB individually based on the investigator’s judgment. In this case, the adverse events should also be notified to the principal investigator. The principal investigator will review the adverse events and take necessary measures including reporting to MFDS and IRBs of other institutions.

1. **Data & Safety Monitoring Plans (DSMP)**

(1) Monitoring Plan

A. Monitoring staff: CRAs of Korean Gynecologic Oncology Group (KGOG)

B. On line monitoring: Monitoring staff will review the data uploaded on the eCRF once a month and send out queries to each institution for any uncertain or erroneous data. The staff will also make requests to the institutions for cases with delayed input.

C. Face-to-face monitoring: Visits will be made when there are 2 subjects and 10 subjects who completed Week 4 visits for each institution and perform monitoring activities according to KGOG monitoring SOP.

(2) Monitoring Frequency

On line monitoring will be conducted once a months and face-to-face monitoring will be conducted 2 times during the trial period for each institution.

(3) Monitoring Result Reporting

A. KGOG will draft monitoring result reports after conducting on line monitoring (monthly) and face-to-face monitoring activities and repot to the principal investigator.

B. The principal investigator will send the report to responsible investigators of applicable institutions and request the investigator to report to IRB.

C. For any matters that require a separate reporting to IRB such as non-compliance, the principal investigator will request the responsible investigator of the institution to report to IRB.

D. The principal investigator can request a corrective plan to each institution’s responsible investigator depending on the contents included in the result report.

1. **Data Analysis and Statistical Analysis Methods**

(1) Information on inter-group univariate comparative analysis is stated under the sections ‘Efficacy Evaluation Standards, Evaluation Methods’ and ‘Evaluation Standards, Methods and Reporting of Safety Including Side Effects.’

(2) In case of inter-group differences for the subjects and surgical information factors, a multivariate comparative analysis will be conducted including the different factors. For example, if there is age difference between A+B arm and C+D arm, a multivariate analysis will be conducted to include the age factor in addition to the univariate comparative analysis.

1. **Trial Schedule**

Enrolment rate: 9/month

Submission date to health authority / ethics: March, 2020

Start of subject enrolment: August, 2020

End of Subject enrolment: March, 2022

End of Study: May, 2023

Report (as described in the contract, e.g. draft publication): Dec, 2023

Planned publication /presentation: Dec, 2023

1. **Measures for Safety and Protection of Subjects**
2. **Basic considerations to ensure ethical conduct of the trial**

The trial will be in compliance with the Declaration of Helsinki (revised in 2013) and ICH-GCP.

The trial will be conducted after obtaining IRB approval.

1. **Process for subjects to express consent**

(1) Investigators who will explain to the subjects and obtain their consent: [name], [name], [name], [name], [name], [name], [name]

(2) Persons who will express their consent: subjects

(3) Waiting period between trial explanation and consent acquisition: 5 minutes

(4) Measures to minimize the possibility of coercion or negative influence: subjects will be explained clearly that there will be no disadvantages even if they do not participate in the trial.

(5) Language to be used by investigators in the process of trial explanation and consent acquisition: Korean

(6) Language that can be understood by the subjects or their representatives: Korean

(7) Information and the consent form provided to the subjects or their representatives: to be submitted as separate documents

1. **Compensations for the subjects**

(1) 30,000 won will be paid out as travel expense for the subjects on their Week 4 visit and Year 1 visit after surgery.

(2) If subjects are withdrawn from the trial, travel expense until the withdrawal will be paid out.

(3) Subject will not be paid for travel expense at baseline visit and hospitalization for surgery because these visits are considered to be related to the subjects’ surgery.

1. **Private information protection of the subjects**

(1) Patient medical record numbers and pathology numbers will be managed in a separate file under the responsibility of the principal investigator which will be coded so that one’s personal information cannot be identified from the trial data.

(2) Trial data is stored on the eCRF which is accessible only with a password.

(3) In accordance with Article 15 of the Enforcement Regulations of the Bioethics and Safety Act, trial-related records should be kept for 3 years from the point the trial is completed. Documents with expired storage period will be shredded according to Article 16 of the Enforcement Decree of the Personal Information Protection Act.

1. **Additional protection measures in case vulnerable population is included**

Vulnerable population is not included in the trial.

1. **Disposal of human body materials**

No human body materials are collected.

1. **References**

Inserted as Pubmed ID in the body of the protocol.

1. **Creating a surgical video for abdominal fascia closure operating using SS-PDS**

1) Subjects can express consent for creating a video optionally.

2) A video will be produced for the abdominal fascia closure technique using SS-PDS for subjects who expressed consent in advance. Any personal information or sensitive body parts should not be included in the video.

3) Even if a subject expressed consent to create a video, he/she may not agree to produce the video later.

4) When a video is produced, the subject will be notified of the production immediately after the surgery. If the subject wants to watch the video, the investigator should cooperate.

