A. investigators: investigators at each institution can view CRF and check randomization results without a separate approval procedure.

B. study subjects: if investigators see it necessary for medical purposes, they can inform the subjects of the randomization results after approval by the principal investigator.

(8) Interim Analysis

A. Interim analysis for the initial safety review

A) When the 10th subject is allocated to A+B arm and finishes his/her Week 4 visit, an evaluation will be performed on 10 subjects in A+B arm for incidence, types, and grades of surgical site infections, wound dehiscence, and other adverse events.

B) Evaluation results will be reported to IRB. If incidence, types, and grades of adverse events are judged to exceed the usual range, possible measures including trial discontinuation will be considered.

B. Interim analysis for wound dehiscence of subcutaneous drain

A) An evaluation will be performed when the 44th subject of A+C arm and B+D arm, respectively, completes his/her week 4 visit.

B) If wound dehiscence incidence of A+C arm is lower than B+D arm (one-sided p < 0.005), it will be decided that subcutaneous drain insertion reduces wound dehiscence and further randomization will be stopped. That is to say that subcutaneous drain will be inserted to all subject from then.

1. **Investigational Product Dosage, Application/Administration Methods, Combination Therapy, and Reasons for Comparator (as applicable)**

(1) SS-PDS arm (fascia closure using SS-PDS)

A. Instructions

A) STRATAFIX Symmetric PDS Plus, suture size: 1/0, suture length: 45cm, needle size: 40mm (CT needle) (Ethicon, Somerville, NJ, USA)

B) Running suture will be used as recommended by the manufacturer and stated in previous studies [PMID: 28603661] (<https://www.youtube.com/watch?v=PTYtYvSaGMg>, <https://youtu.be/TPyulS4fQgQ>)

C) Peritoneum closure should be performed. If peritoneum closure is impossible due to peritoneotomy, it may not be performed.

D) For fascia closure, stiches will be made 5-8 mm apart including 5-8 mm thick tissues on both sides of the incision surface.

E) It is allowed to make additional stiches for fascia closure with a few interrupted sutures using PDS or other sutures based on the investigator’s judgment.

F) Suture length is recommended to be 4 times longer than the skin incision. That is, if the skin incision is 20cm, it is recommended to use 80cm or longer suture for closure.

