G) Cares should be made to stitch only the aponeurosis located at the ventral rectus muscle and not to stitch too much fat tissues or muscles. It is recommended to include dorsal sheath of the rectus muscle in the stiches from the cephalic side of the arcuate line, if possible.

H) It is recommended to start the stiches from cephalic end and caudal end of fascia incision. That is, the stiches should not be ended at the caudal end (fascia touching the public bone).

I) If the stiches end in the middle of the incision, additional stiches should be made 2-3 times in reverse direction as recommended and finished. Also, there should be an overlap of 2cm or longer with the next suture.

F) Stitching can start from one side of the incision wound if necessary (Appendix Figure 1)

G) Since barbed suture does not become loose after stitching unlike general suture, the suture should not be pulled hard for closure. Also, constant force should be applied for the closure so that the pressure is evenly distributed over the stitches.

B. Reasons for selection

The reasons are stated under the section ‘Background.’

(2) SS-PDS control group (fascia closure using conventional sutures instead of barbed suture)

A. Instructions

A) PDS Plus, suture size: 1/0, suture length: 90cm, needle size: 40mm (CT needle) (Ethicon, Somerville, NJ, USA)

B) Running suture will be used as stated in previous studies [PMID: 26188742]

C) Peritoneum closure should be performed. If peritoneum closure is impossible due to peritoneotomy, it may not be performed.

D) For fascia closure, stiches will be made 5-8 mm apart including 5-8 mm thick tissues on both sides of the incision surface.

E) It is allowed to make additional stiches for fascia closure with a few interrupted sutures using PDS or other sutures based on the investigator’s judgment.

F) Suture length is recommended to be 4 times longer than the skin incision. That is, if the skin incision is 20cm, it is recommended to use 80cm or longer suture for closure.

G) Cares should be made to stitch only the aponeurosis located at the ventral rectus muscle and not to stitch too much fat tissues or muscles. It is recommended to include dorsal sheath of the rectus muscle in the stiches from the cephalic side of the arcuate line, if possible.

H) Stitches can start from both ends or one end of fascia incision. In case of using 2 sutures, each suture should be fixed with a knot, respectively, and stitches should be overlapped for more than 2cm.

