2. Subcutaneous tissue closure is not necessary, but can be performed based on the investigator’s judgment.

3. Skin closure can be performed using stapler or non-absorbent sutures whichever is a general method of each institution.

B. Reasons for the choice

The reasons are stated under the section ‘Background.’

1. **Observation Items, Clinical Test Items, Observation and Test Methods**

| Observation Items | Observation and Test Methods |
| --- | --- |
| 1-year cumulative incidence of incisional hernia after surgery | Subjects are advised to make outpatient visits for Year 1 after surgery. Visits made between 9 and 15 months after surgery can be counted as Year 1 visit. Investigators will conduct a physical checkup to diagnose incisional hernia. Investigators can refer to post-surgery image test result. If investigators are not sure of incisional hernia, a diagnostic test can be carried out. Subjects will be censored if they underwent midline laparotomy once again after receiving the surgery from this study, are dead or lost to follow-up at the time of event. Investigators will not be reminded of group allocation and will be blinded until Year 1 visit is completed. |
| 4-week cumulative incidence and types of surgical site infection after surgery | Subjects are advised to make outpatient visits for Week 4 after surgery. Visits made between 3 to 5 weeks after surgery can be counted as Week 4 visit. Investigators will conduct a physical checkup to diagnose surgical site infection. If subjects make outpatient visits before Week 4 after surgery, investigators should check for surgical site infections and their types. All information obtained from visits made immediately after surgery up to Week 4 will be used to diagnose all surgical site infections. CDC standards will be used to determine surgical site infections and their types. (https://www.cdc.gov/nhsn/PDFs/pscManual/17pscNosInfDef_current.pdf). If any surgical site infection is observed according to CDC standards, the patient will be judged to have a surgical site infection. Investigators will not be reminded of group allocation. |

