**(1) Causality Evaluation**

A. Investigators will determine that there is or there is no causal relationship with the SS-PDS use (including control group’s suture). If it is difficult for the investigator to make a judgment, it will be judged to have a causal relationship.

B. Causality will not be evaluated for the use of subcutaneous drain.

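### The 7-day safety report covers serious, unpredicted, suture-related events in the SS-PDS arm only; the same event in a control patient has no mandatory route before the yearly collection

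*Protocol*

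**What the plan says.** Item A of Reporting Methods defines the expedited class as "Adverse events from SS-PDS arm that are serious, unpredicted and in causal relationship (SS-PDS SUSAR"). For this class, "Investigators will take below measures in 7 days from the day they became aware of such adverse events": a report to the site's own IRB and a report to the principal investigator. KGOG then has a further 7 days to report to MFDS and informs the other institutions so that their IRBs are told. The last line of item A asks for a direct report to the principal investigator when such events are fatal or life-threatening.

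Item B covers everything else. KGOG "will collect all adverse events from all participating institutions once a year and report to IRBs of all the participating institutions". Earlier individual reporting is optional: "Adverse events that are not SS-PDS SUSAR can also be reported to IRB individually based on" the investigator's judgment.

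Causality Evaluation is wider. It says "Investigators will determine that there is or there is no causal relationship with the SS-PDS use", and the same sentence adds the control group's suture. A case that is hard to judge counts as related.

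On blinding, the incisional hernia row of the Observation Items table says: "Investigators will not be reminded of group allocation and will be blinded until Year 1 visit is completed".

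**The concern.** Both groups receive an assigned fascia suture, and the investigator must decide for both whether an event is related to it. In the SS-PDS arm a positive answer on a serious, unpredicted event starts a 7-day clock. In the control group it starts nothing mandatory, even if the event is fatal. What is at stake is prompt notice of a rare but grave event to the principal investigator and the IRBs.

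There is a smaller second issue. A rule that depends on the arm makes the reporting investigator establish the arm, although the Protocol wants those who diagnose hernia not to be reminded of it before Year 1.

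**Working it through.** No arithmetic beyond a sum of deadlines applies. The check is to set the sections side by side.

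1. **Who is in the SS-PDS arm.** In the section on the investigational product and its application, item (1) is headed "SS-PDS arm (fascia closure using SS-PDS") and item (2) "SS-PDS control group (fascia closure using conventional sutures instead of barbed suture"). The first term means the barbed-suture group (A+B). The comparator (C+D) has its own name, so the wording of item A does not include it.

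2. **Whose causality is judged.** Causality Evaluation and all four items of Evaluation Methods add the control group's suture when they mention suture causality. Item A of Reporting Methods does not.

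3. **Route for the same event** (serious, unpredicted, judged related to the suture):

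| Step | SS-PDS arm (A+B) | Control group (C+D) |
|---|---|---|
| Site IRB and principal investigator | Required within 7 days of awareness | Optional, no deadline |
| MFDS, through KGOG | Required within 7 more days, so at most 7 + 7 = 14 days from awareness | Only if the principal investigator decides so after an optional report |
| Fatal or life-threatening | Direct report to the principal investigator | Not covered |
| Mandatory fallback | Not needed | Yearly collection, so up to 12 months at worst |

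4. **Earlier sight of a control event.** Item B allows an individual IRB report. If one is made, the principal investigator must be told and reviews it. Under Data & Safety Monitoring Plans, KGOG also reviews eCRF data monthly and reports its monitoring results to the principal investigator. Either could bring the event forward. Neither is stated as an expedited safety route.

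5. **Dependence on the arm.** Item A cannot be applied without knowing the allocation. Under Control Group Setting and Randomization, the SS-PDS allocation is kept out of the medical records and held on the CRF. Yet the site hears it by phone just before fascia closure, and investigators may check it on the CRF without separate approval. The rule is therefore workable, but applying it prompts the reminder that the Observation Items table sets out to avoid.

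6. **How many events qualify.** The Protocol gives no rate. Benefits for and Risks to Subjects lists wound infection, wound complication, wound dehiscence, and abdominal and peritoneal infection as predictable. For the barbed suture it adds more incisional hernia, surgical site infection, dehiscence and pain as potential risks. If unpredicted is read against these lists, the usual wound failures do not reach item A in either arm. Among 174 patients (87 per group), what is left is probably few events.

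**The case against.** The asymmetry can be defended as deliberate. The Overview names SS-PDS alone as the investigational product. The risk section says there is little clinical experience with it in abdominal fascia closure, while slowly absorbed sutures are described as an accepted standard. The early safety review covers ten A+B subjects only, and the first discontinuation rule refers to the safety of SS-PDS. Judging causality in both groups feeds the adverse-event comparison and does not by itself require expedited reporting in both. Whether regulation requires it for a comparator cannot be settled from the Protocol. This explains the wording, but it gives no reason to leave a fatal, unpredicted event judged related to the control suture without any prompt mandatory report.

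It is also fair to say that a 12-month wait is a worst case, and that assessor blinding is already weak because of the phone notification and the open CRF access. Both points stand. Rewording the reporting rule would not repair the blinding; it would only remove one needless prompt to look up the arm.

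Three stronger readings are tempting, and the Protocol does not support them:

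- A reader might infer that about half of all qualifying events miss the expedited route. That follows only from assuming equal rates in equal groups and no discretionary reports; no rate is given.
- A reader might infer that the rule unblinds precisely the patients whose wounds fail. The usual wound failures are listed as predictable and can be ruled out without knowing the arm.
- A reader might infer that events will look concentrated in the SS-PDS arm to those who can stop the trial. The yearly report covers all adverse events from all institutions, and readers of the Protocol would know that the expedited reports come from one arm.

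**Conclusion.** The gap is real and narrow. A serious, unpredicted event judged related to the suture must be reported within 7 days in the SS-PDS arm. In the control group it has no mandatory route before the yearly collection, and the fatal or life-threatening clause does not close the gap. The need to know the arm is a side effect, secondary to the open CRF access.

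This rests on reading the SS-PDS arm as A+B, which the Protocol's own headings support, and on reading unpredicted against its lists of predictable risks. The number of events affected cannot be computed from the Protocol and is probably small. No effect on the primary analysis, alpha or power is shown. Low priority, but worth correcting because the change is cheap.

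**What to change.** Reword item A of Reporting Methods to cover serious, unpredicted events judged related to the study suture in either arm, using the same scope as Causality Evaluation. Let the site report without stating or looking up the arm. KGOG, which performs the randomization and holds the result, adds the allocation when it reports onward. Keep the timelines and the fatal or life-threatening clause, which would then apply to both groups. Change the SS-PDS SUSAR label in items A and B to match, so that item B again holds only what falls outside the expedited class.

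The cost is a wording amendment and a few extra expedited reports from the control arm. Treatment, visits and sample size do not change.

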**Appendix Figure 1**

[figure not shown]

[figure not shown]

[figure not shown]

Supplement: S5 File — (DOCX) [file pone.0337036.s005.docx]
